### Data collection

The enumerators were recruited from Noguchi Memorial Institute for Medical Research (NMIMR) and Institute of Statistical, Social and Economic Research (ISSER), and trained for the baseline survey. Each team, led by a supervisor and assisted by community leaders conducted household listings and sampling in each enumeration area (EA). Maps were obtained for most of the EAs from the Ghana Statistical Service. The EA maps made it possible to identify all dwelling structures within a geographical space with a well-defined boundary. All dwelling/housing structures within each EA were serially numbered to facilitate the complete listing of households. The list of households in each EA constituted the sampling frame from which participating households were selected at random for the interview. A total of 2626 households in 116 communities were surveyed (see Table 5 for the data collection coverage) between the 22 June and the 2 September 2013.

**Table 5 Tab5:** Household data collection coverage

Region	Communities	Number of households		
		Intervention	Control	Total
Western	8	96	80	176
Central	6	75	60	135
Greater Accra	2	24	25	49
Volta	10	123	101	224
Eastern	6	75	60	135
Ashanti	18	225	180	405
Brong-Ahafo	12	150	120	270
Northern	26	319	284	603
Upper East	10	225	179	404
Upper West	10	125	100	225
Total	116	1437	1189	2626

In each household, all children aged between 5 and 15 years were asked education-related questions (enrolment, attendance, drop-out) and were tested in literacy, maths, forward and backward digit span and Raven’s matrices. Anthropometry measurements were undertaken for children aged 2–15 years. Tests and measurements were made at the household level because not all the children in the targeted schools resided in the selected localities where the schools were situated. Height measurements were taken with Leicester Height Measures and weights were measured using Tanita Electronic Scales WB-100A/WB-110A Remote Display Version scales, which allow height measurements of up to 2 m 10 cm to the nearest 1 mm. The height and weight measures were assembled and placed on a level surface. In the absence of a level ground in the household, a suitable place was identified for the measurement in the community. A sub-set of children aged 5–15 years were randomly selected for haemoglobin and parasitology measurements. Haemoglobin levels were collected using HemoCue Hb 201+ analyser, with standard controls reagents (Hemotrols) used to verify appropriate device function on a daily basis.

### Data management and analysis

All questionnaires were checked in the field for consistency and completeness by field supervisors before data entry. Data were entered in CSPro and later transferred to Stata 12 for data cleaning and analysis. Simple frequency tables of variables from each module in the questionnaire were generated from the database and examined for inconsistencies. Errors related to wrong entries were verified from the specific questionnaire and corrected appropriately.

### Ethical approval

Ethical clearance was obtained from the Institutional Review Board of the Noguchi Memorial Medical Research Institute of the University of Ghana and sought at the Imperial College Research Ethics Committee. Meetings were held from early stages in the study development with relevant government ministries both at central and decentralised levels to discuss the purpose, procedures and risks involved in the study. Informed consent was obtained from parents/guardians of children through written and verbal information provided before interviews.

## Results

Table 6 summarises the characteristics for key variables of interest in the study population and by study group. We also report the main evaluation comparisons, including school feeding (combined GSFP and HGSF) versus control (no school feeding), regular school feeding (GSFP) versus HGSF (combined HGSF+ and HGSF++) and HGSF with micronutrient sprinkles (HGSF++) versus HGSF without sprinkles (HGSF+). The tests of balance show evidence of small differences across the treatment arms for several variables across education, nutrition, agriculture and other socio-economic domains. In addition, approximately 19 % of children in the target age group (5–15 years) received some form of free school meals at baseline. Of the total 8407 children aged 15 years or younger, 48 % were girls.

**Table 6 Tab6:** Key baseline characteristics of participants for all individuals and households by study group, Ghana baseline survey

			Control (C)		School feeding (SF)								
					Ghana SF Programme (GSFP)		‘Home-grown’ school feeding (HGSF)				Main evaluation comparisons*		
	All						HGSF+		HGSF++		Ha: [*A − B*] ! = 0, Pr(|*T*| > |*t*|)		
Characteristic	*n*	Estimate	*n*	Estimate	*n*	Estimate	*n*	Estimate	*n*	Estimate	[SF − C]	[GSFP − HGSF]	[HGSF+ − HGSF++]
Outcomes													
Absentee days over last 7 days	6217	0.130 [0.678]	2754	0.121 [0.672]	1765	0.117 [0.613]	855	0.186 [0.790]	843	0.130 [0.685]	0.327	0.0745	0.1227
Age started school (aged 5–15 years)	3907	7.18 [1.95]	1734	7.16 [1.92]	1105	7.36 [1.88]	560	7.18 [2.05]	508	6.86 [2.07]	0.5276	0.0001	0.0123
Number of times repeated a class	6067	0.23 [0.62]	2677	0.21 [0.57]	1726	0.25 [0.62]	825	0.26 [0.67]	839	0.22 [0.72]	0.0356	0.7323	0.2238
Maths test score	5826	2.51 [2.79]	2588	2.31 [2.70]	1646	2.54 [2.75]	801	2.91 [3.04]	791	2.74 [2.87]	<0.001	0.004	0.2756
Literacy test score	5849	3.06 [3.69]	2596	2.75 [3.50]	1661	3.05 [3.56]	804	3.58 [4.07]	788	3.57 [4.06]	<0.001	<0.001	0.9423
Raven’s test score	5830	4.46 [2.74]	2590	4.32 [2.75]	1650	4.52 [2.69]	800	4.84 [2.70]	790	4.41 [2.81]	<0.001	0.2448	0.002
Digit span score	5883	4.78 [2.40]	2615	4.56 [2.40]	1664	4.89 [2.37]	809	5.13 [2.39]	795	4.89 [2.39]	<0.001	0.152	0.0487
Height-for-age (5–15 years) z-score	5232	−0.925 [1.35]	2303	−0.943 [1.43]	1494	−0.963 [1.29]	730	−0.888 [1.24]	705	−0.827 [1.31]	0.3999	0.0268	0.3666
BMI-for-age (5–15 years) z-score	5232	−0.592 [0.924]	2303	−0.575 [0.964]	1494	0.636 [0.895]	730	−0.574 [0.857]	705	−0.570 [0.912]	0.2542	0.051	0.9284
Haemoglobin levels (g/dL)	714	11.3 [1.34]	422	11.3 [1.35]	169	11.3 [1.36]	32	11.4 [1.47]	91	11.3 [1.21]	0.9088	0.8764	0.8469
Total maize production volumes (kg)	2626	787 [1751]	1163	864 [2034]	722	807 [1596]	375	590 [1248]	366	702 [1478]	0.0439	0.0376	0.2646
Total rice production volumes (kg)	2626	141 [652]	1163	149 [700]	722	148 [645]	375	137 [678]	366	111 [449]	0.6003	0.4551	0.5297
Total maize sale volumes (kg)	2626	393 [1196]	1163	432 [1261]	722	446 [1337]	375	270 [880]	366	292 [907]	0.1381	0.0057	0.7435
Total rice sale volumes (kg)	2626	84 [484]	1163	94 [583]	722	87 [413]	375	70 [397]	366	61 [327]	0.3509	0.2895	0.7286
Other variables													
Age (for 15 years and younger)	8407	7.5 [4.2]	3153	5.8 [9.0]	1918	6.2 [9.5]	942	6.2 [9.3]	917	6.1 [9.9]	0.057	0.847	0.8071
Is a girl? (for 15 years and younger)	8407	0.48 [0.5]	3799	0.48 [0.50]	2318	0.49 [0.50]	1167	0.47 [0.50]	1123	0.51 [0.5]	0.4933	0.9377	0.0989
Birth order (for all children)	8533	2.9 [2.0]	3791	2.9 [2.1]	2397	3.0 [2.0]	1189	3.0 [2.0]	1156	2.9 [1.9]	0.8275	0.021	0.2204
Is enrolled in school? (for 5–15 years)	6178	0.92 [0.27]	2755	0.91 [0.29]	1737	0.92 [0.26]	852	0.94 [0.01]	834	0.91 [0.29]	0.0375	0.9395	0.0065
Receives free school meals?	6280	0.19 [0.39]	2809	0.17 [0.38]	1768	0.23 [0.42]	860	0.13 [0.34]	843	0.24 [0.43]	0.0001	0.0055	<0.001
Distance to nearest school	6343	0.47 [3.24]	2765	0.45 [3.14]	1808	0.58 [4.34]	891	0.21 [0.85]	879	0.59 [2.29]	0.597	0.0992	<0.001
Time to school	6333	21.4 [45.6]	2778	19.6 [31.3]	1796	18.8 [32.5]	888	17.6 [22.7]	871	35.9 [95.1]	0.007	<0.001	<0.001
Total education expenditure	5635	23923 [35642]	2410	19250 [30878]	1640	27089 [37899]	789	25732 [37096]	796	29752 [40791]	<0.001	0.6249	0.0403
Mother’s education level (5–15 years)	5096	5.9 [9.4]	2290	5.7 [9.1]	1437	6.1 [9.6]	690	6.1 [9.4]	679	6.0 [9.8]	0.1946	0.8518	0.7608
Education level of head of household	2626	1.4 [2.6]	1163	1.4 [2.7]	1463	1.3 [2.5]	375	1.6 [2.7]	366	1.3 [2.2]	0.9393	0.2147	0.1344
Household size	2626	5.7 [2.4]	1163	5.7 [2.4]	722	5.8 [2.4]	375	5.7 [2.3]	366	5.6 [2.3]	0.8747	0.1774	0.5572
Per-capita expenditure quintile	2625	3.1 [1.4]	1162	3.2 [1.4]	722	2.9 [1.4]	375	3.3 [1.4]	366	3.1 [1.4]	0.1763	0.0008	0.2199
Household expenditure on food	2626	3473 [2187]	1163	3483 [2213]	722	3370 [2254]	375	3502 [1846]	366	3608 [2289]	0.815	0.1041	0.4874
Household expenditure on health	2626	93.5 [112]	1163	97.7 [116]	722	88.7 [107]	375	93.3 [108]	366	90.0 [112]	0.0894	0.595	0.6768
Household expenditure on education	2626	214 [333]	1163	204 [328]	722	195 [311]	375	233 [340]	366	260 [374]	0.1926	0.0034	0.3013
Household expenditure on transport	2626	317 [415]	1163	315 [407]	722	297 [393]	375	352 [447]	366	326 [447]	0.8157	0.0607	0.4316
% share of HH expenditure spent on food	2626	59.8 [15.8]	1163	59.6 [16.4]	722	60.3 [15.4]	375	58.0 [14.0]	366	61.1 [16.0]	0.5613	0.3073	0.0049

Estimates are expressed as mean and standard deviation

*BMI* body mass index, *HH* household. * T-test statistics for comparisons across treatment arms

In the education domain, 92 % of children aged 5–15 years were enrolled in school, and mean enrolment rates were marginally lower in the control population (0.91, SD 0.29) compared to the school feeding group (0.93, SD 0.26). Significant differences were also found for age of first enrolment, the number of times that a year was repeated, and across all the four test scores.

In the nutrition domain for children aged 5–15 years, the mean z-scores for the anthropometrics measures of height for age and BMI for age were −0.925 (SD 1.35) and −0.592 (SD 0.924) respectively, with significant differences across the GSFP versus HGSF comparison groups. Iron status, as measured through haemoglobin levels, for the sub-sample of children (*n* = 714) who were assessed, was on average 11.3 g/dL (SD 1.34), just below the 11.5 g/dL cut-off for non-anaemia in the 5–11 years age group.

In terms of household socio-economic characteristics, there were neither significant differences among the treatment groups for the mean education levels of mothers and household heads, nor for household size. There was, however, a significant difference in terms of per-capita household expenditure quintiles between households in the GSFP and HGSF groups, but no other substantive differences with regards to household expenditure were observed.

In the agriculture domain, across the survey population the mean production of maize over the previous 12 months was 787 kg (SD 1751), with average household sales of maize during the same period of 393 kg (SD 1196). Mean household production of rice was 141 kg (SD 625), with average annual sale volumes of 84 kg (SD 484). Significant differences were found across treatment arms in terms of maize production and sales.

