### Random assignment and manipulation of treatments

Households and schools were randomly assigned to three treatment arms:Control group: these are schools and households from communities where the intervention will not be implemented. The intervention will be delayed by at least 3 years in these communities, preferably without informing schools and households. After the 3- year period, these schools will be covered by the GSFP.Regular GSFP group: these are schools and communities where the standard GSFP is implemented, with caterers responsible for the food procurement and preparationHGSF+ group: these are schools and communities where the programme is implemented in addition to a pilot capacity-building component, including training of community-based organisations and other stakeholders, on food procurement, nutrition education, and feedback monitoring. This group will be randomly divided into two sub-groups (HGSF+ and HGSF++) as part of a study focussing on anaemia.

Note that the HGSF+ intervention will be conducted at the district level. Training and monitoring systems involve caterers and exert their effects at the district level, affecting outcomes in schools where the HGSF+ programme is not implemented. On the other hand, the number of districts where the programme is implemented is rather small, which reduces the statistical power of the analysis, and the effects of the school feeding intervention against the control group are best observed at the school level. Hence, we opted for a design that compares the outcomes of the school feeding and control groups at the school level, and that compares outcomes of HGSF+ and regular school feeding (GSFP) at the district level.

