### Study area and site selection

Selection of the target areas involved three key steps: 1) the first step involved selecting 58 districts at random within Ghana from a sample frame including all districts in the country. The sample frame was stratified by region, and district inclusion was prioritised using data from the GSFP retargeting exercise including data on the prevalence of poverty and food insecurity; 2) the second step involved identifying 2 comparable schools within each of the 58 selected districts. A list was obtained through the GSFP secretariat including schools not currently covered by the GSFP in each district. Data from the annual school census from 2011 to 2012 were then used to match schools not receiving the GSFP and identify ‘best matched’ pair. The allocation of school feeding and control was then randomised (lottery style) within each pair; 3) the third step in the site selection protocol involved the random allocation of districts to the HGSF+/GSFP groups by modelling pilot selection using a set of community- and district-level variables and selecting the permutation of allocation that minimises the *R*^*2*^ for the predicted selection [13].

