In addition, approximately 19 % of children in the target age group (5–15 years) received some form of free school meals at baseline. Similar findings were reported in a similar study in Mali in 2013 by Masset and Gelli [13] where, because of information flow constraints, the original list of schools used in the randomisation included schools with school feeding. This finding has important implications in terms of the evaluation design, considerably reducing sample sizes available for comparisons after the follow-up survey. The small sample sizes between the HGSF+ and HGSF++ comparisons are a particular concern, and power calculations using the baseline data suggest folding these two arms into one, adding micronutrient sprinkles to the HGSF+ intervention.

Significant differences were found in the means of a number of outcome and control variables across the intervention groups. It appears, therefore, that at baseline the random allocation process did not achieve statistically comparable treatment groups. In particular, important differences across groups include marketed surplus, livestock income, per capita food consumption and intake, school attendance, anthropometric status in the 2–5 and 5–15 years age groups. Differences in outcome and control variables across groups will be controlled when estimating treatment effects. More in-depth analyses of the very rich baseline dataset, examining the associations between key outcomes and variables along the complex agriculture-nutrition are also underway.

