### Power calculations

#### School attendance

We used the rural sample of the GDHS data of 2008 to estimate attendance rates of children in the age group 6 to 14 and we found rates of 79 % for boys and 81 % for girls. The chart below plots values of power for increasing number of clusters assuming a project impact of 5 percentage points on attendance rates in primary school. A sample of just 60 clusters and collecting data on 40 children is sufficient to detect such an impact with 80 % statistical power (Fig. 4).

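### The control is described as having no school feeding although 17% of its children already received free school meals, and the diluted contrast is not carried into school feeding v control

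*Protocol article*

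**What the plan says.** The section on random assignment defines the comparator by what is withheld: "Control group: these are schools and households from communities where the intervention will not be implemented". Under site selection, candidate schools came from a frame meant to exclude existing provision: "A list was obtained through the GSFP secretariat including schools not currently covered by the GSFP in each district". The Results section then names the first main comparison as "school feeding (combined GSFP and HGSF) versus control (no school feeding".

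Table 6 reports actual receipt in the row "Receives free school meals": control 0.17 (n = 2809), GSFP 0.23 (n = 1768), HGSF+ 0.13 (n = 860) and HGSF++ 0.24 (n = 843). The article is open about the overall figure, which appears in the abstract, the Results and the Discussion: "approximately 19 % of children in the target age group (5–15 years) received some form of free school meals at baseline". The Discussion gives the consequence as "considerably reducing sample sizes available for comparisons after the follow-up survey". The only recalculation it reports concerns HGSF+ v HGSF++, where "power calculations using the baseline data suggest folding these two arms into one".

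Appendix 1 sizes attendance by "assuming a project impact of 5 percentage points on attendance rates in primary school" and, for the other outcomes, tabulates standardised detectable differences at 30, 60 and 120 clusters. The Methods of analysis section plans intention-to-treat together with per-protocol and as-treated analyses.

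**The concern.** The comparator's description in the Results conflicts with the article's own baseline table. Delaying the GSFP in control schools does not by itself remove meals that children there already get from some other source, or because the frame was out of date. The Discussion likens the finding to a study in Mali where the school list itself contained schools with feeding.

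Under intention-to-treat, fed control children stay in the control arm. The consequence is then a smaller difference in exposure between the arms, which is a different problem from losing sample and is not discussed. The trial estimates the programme against usual provision that includes some free meals. Anyone who takes the comparator at its word would read the result, and the detectable differences, as meals v none.

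**Working it through.** **Inputs.** Meal receipt is from Table 6. ICCs and cluster sizes are from Appendix 1: Raven's 0.14 and 40; haemoglobin 0.13 (children) or 0.08 (mothers) and 20; height-for-age 0.08 and 30. Allocation is 1:1. Two-sided 5% is my assumption, since no alpha is stated; it reproduces the tables.

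**Step 1: baseline exposure.** Feeding arms: (0.23×1768 + 0.13×860 + 0.24×843)/3471 = 720.8/3471 = 0.208. Adding control, (720.8 + 0.17×2809)/6280 = 0.191, which matches the stated 19%.

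**Step 2: reproduce Appendix 1.** With K clusters in total and m children per cluster, the detectable difference is (t₀.₉₇₅ + t₀.₈₀ on K−2 df) × √{2[1+(m−1)ICC]/((K/2)m)}.

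| Outcome | Printed, 30/60/120 clusters | Recomputed |
|---|---|---|
| Raven's | 0.43 / 0.30 / 0.21 | 0.426 / 0.296 / 0.207 |
| Haemoglobin, children | 0.44 / 0.31 / 0.21 | 0.442 / 0.307 / 0.215 |
| Haemoglobin, mothers | 0.38 / 0.26 / 0.18 | 0.376 / 0.261 / 0.183 |
| Height-for-age | 0.35 / 0.25 / 0.17 | 0.353 / 0.245 / 0.172 |

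The tables follow from ICC, cluster size and cluster number alone. They are between-arm differences, and nothing in them depends on what control children eat. Farm income cannot be reproduced because its ICC is not given as a number.

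**Step 3: convert to an effect of being fed.** Let d be endline coverage in the feeding arms minus coverage in control. If existing meals have the same effect as programme meals, a fed-v-unfed effect δ appears between the arms as dδ. The detectable δ is the tabulated value divided by d. An effect sized for 80% power has power Φ(2.802d − 1.960), where 2.802 = 1.960 + 0.842.

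- Control 17%, feeding arms 100%: d = 0.83, 1/d = 1.20, power Φ(0.366) = 64%.
- Control 10%: d = 0.90, power 71%.
- Control 5%: d = 0.95, power 76%.
- Control 17%, feeding arms 90%: d = 0.73, power Φ(0.085) = 53%.

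At d = 0.83 and 120 clusters, Raven's goes from 0.207 to 0.250 SD, children's haemoglobin from 0.215 to 0.259 and height-for-age from 0.172 to 0.207. At the 116 schools enrolled the values are 0.211 to 0.254, 0.219 to 0.263 and 0.175 to 0.210. The haemoglobin and height-for-age planning values come from under-fives; I use them, as the article does, as planning figures for the trial.

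**Step 4: the one stated power.** Attendance has 80% for 5 points at 60 clusters of 40, with no ICC. From 80% to 85%, 906 children per arm are needed without clustering. The implied ICC is (1200/906 − 1)/39 = 0.008 if 60 is the total, or (2400/906 − 1)/39 = 0.042 if 60 is per arm. At 116 schools and d = 0.83, power is Φ(2.802×0.83×√(116/60) − 1.960) = 90% on the first reading. On the second it is Φ(2.802×0.83×√(116/120) − 1.960) = 63%.

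**Step 5: sample loss is not the same thing.** Losing 19% of clusters multiplies detectable differences by 1/√0.81 = 1.11 (power 71%). Losing 19% of children within clusters barely matters: for Raven's, √[(5.396/32.4)/(6.46/40)] = 1.02. Neither equals the 1.20 from dilution.

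**The case against.** The strongest reply is that Appendix 1 never claims to size a fed-v-unfed effect. It speaks of a project impact and tabulates differences between arms, and Step 2 confirms that those are arithmetically right whatever the control children eat. This stands. A reader might infer that the printed detectable differences hold only for an unfed control, or that the stated power is too high; the document supports neither. The only stated power is for 60 clusters against 116 schools enrolled, and if 60 is the total it exceeds 80% even after dilution. The missing ICC leaves the other reading open but does not establish it.

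The size is also conditional. The 17% was measured in 2013, before the intervention, and the follow-up is planned for November 2015. The article says only that meals of some form were received, so equal effect is assumed. Subtracting the feeding arms' 21% baseline receipt gives a difference-in-difference contrast of 0.79 and, by the same formula, 60% power. But Appendix 1 contains no power calculation for that estimator, whose variance differs, so I do not rely on it. Farm income should not be scaled either, because its pathway runs through caterer procurement and not through children's meal receipt.

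Finally, the baseline meals are disclosed, in the same paragraph as the comparator's label, and an as-treated analysis is planned. Disclosure does not correct the label or quantify the consequence for school feeding v control, and an as-treated comparison gives up the randomised contrast.

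**Conclusion.** The point holds in a limited form. The comparator's description conflicts with Table 6, and the consequence under intention-to-treat, a smaller exposure contrast, is neither named nor quantified for school feeding v control. The Appendix 1 figures are not in error; they simply do not describe the trial's sensitivity to meals v no meals.

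With 17% residual feeding in control, full coverage in the feeding arms and equal meal effects, detectable effects of being fed are about 1.20 times the printed ones: Raven's 0.21 to about 0.25 SD and height-for-age 0.17 to about 0.21 SD at 120 clusters. An effect sized for 80% power would have about 64%, or 71% and 76% if residual control feeding is 10% and 5%. Incomplete coverage in the feeding arms would make this worse, and weaker existing meals would make it better. A reader might take 64% as the trial's actual power. It is the power against a hypothetical fed-v-unfed effect equal to the detectable difference, under those three assumptions.

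**What to change.** 1. In the Results, describe the control as usual provision, with 17% of children receiving free school meals at baseline, and interpret intention-to-treat against that comparator. The abstract describes delayed implementation and needs no such correction.
2. In Appendix 1, state that the printed values are between-arm differences, and add a column for the effect of being fed, divided by the assumed contrast (0.83, with 0.90 and 0.95 as alternatives) and with the assumptions listed. Leave farm income out of that column.
3. Repeat the household questionnaire's item on school meals at the follow-up survey. Beside intention-to-treat, and instead of relying on the as-treated analysis, report the effect of meal receipt with random assignment as the instrument. Make this primarily a GSFP v control estimate: HGSF+ assignment also acts through training, and HGSF++ through fortification as well, so pooling those arms would not isolate meals.

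The cost is some wording, one appendix column and one further analysis on an item already in the questionnaire, with no extra sample. The instrumented interval will be wider than the intention-to-treat interval, by roughly 1/0.83 = 1.20 at that contrast, and wider again because the GSFP arm has only 29 schools.
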